### Sample size

The sample size calculation is based on a success rate of surgery (defined as Engel 1A or 1B at 1 year) in the control group (tailoring based on spikes) of 65 %, and the expected success in the experimental group (HFOs) of 80 %. The resulting margin is 15 %. Using a 1-sided 95 % confidence interval and a non-inferiority limit of 10 %, to acquire an 80 % power we need 39 patients per group. This results in a total of 78 patients. We anticipate that 80 % of the eligible patients will participate in the study.

We expect the potential loss-to-follow-up after the initial intervention to be low. Routine clinical visits to the neurosurgeon and neurologist are scheduled after surgery at 6 to 8 weeks, 6 months and 12 months. Our FU questionnaires coincide with these visits. Inclusions will proceed until the target sample size is achieved to address loss to follow-up. Loss to follow-up can be expected from; 1) withdrawal by the subject from the study during follow-up before the first preliminary outcome determination at 6–8 weeks, and 2) withdrawal from the study during the surgery by the surgeon or dedicated team due to urgent medical or technical issues.

Subjects are replaced if they withdraw from the study during follow-up before the first preliminary outcome determination at 6–8 weeks. Subjects who are withdrawn from the study during the surgery by the surgeon or dedicated team due to urgent medical or technical issues are also replaced.

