### Randomization

Eligible epilepsy surgery patients and/or parents or caregivers will be informed about this study by the researcher in person, minimally 2 weeks in advance of the surgery. Informed consent is asked on the day prior to the day of surgery. After written consent, the patient will be randomized into the treatment allocation (ALEA version-release 2.2). Stratification for participating site and epilepsy type (extra-temporal versus temporal lobe epilepsy) is performed using block randomization of 2, 4 and 6 patients. The stratification for participation site includes an indirect stratification for age, as in the VUmc only adults and in the University Medical Center Utrecht (UMCU) predominantly children are operated on.

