### Statistical methods

The primary “intention-to-treat” analyses at study completion are based on the difference between the treatment arms with respect to surgical outcome after 12 months. The primary outcome is a categorical outcome, seizure freedom versus seizure recurrence. Risk ratios (RR) and risk difference with 95 % confidence interval will be calculated (*X*^2^- test, 1-sided). Secondary outcomes are the amount of tissue resected, neurological deficits, duration of surgery, complications, cognition and quality of life. For the secondary outcome parameters consisting of continuous variables, a *T*-test with 95 % confidence interval is calculated and tested (1-sided). For the secondary outcome parameters consisting of categorical variables, the RR and risk difference with a 95 % confidence interval are calculated and tested using a Chi-square test (1-sided). Logistic regression analysis will be performed: 1) to adjust for the stratification factors, by including site and epilepsy type as variables in analysis, and 2) to investigate if there are relations between seizure outcome and subject variables, such as age, gender, and pathology, or with experimental variables, such as the operating surgeon and the amount of anesthesia received. Note that we are not going to use a mixed model to adjust for site, as we consider two sites too small a sample to be representative for other sites. Regression analysis is also performed between seizure outcome and the secondary outcome parameters.

In the logistic regression analysis we will, after screening of the number of missing data, perform multiple imputation. For the primary and secondary endpoint no imputation will be performed. Statistical analysis will be performed in SPSS version 21 (SPSS Inc., Chicago, IL, USA) or higher and/or R version 3.1 or higher.

The number of eligible patients withholding consent will be registered, and demographic information will be collected anonymously for post-hoc explorative analysis to understand potential bias in study outcomes.

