Our power calculation is based on estimated success rates deduced from retrospective studies up until 2013. These studies consisted of different patient populations. The current success rate of epilepsy surgery based on the old treatment, tailoring based on spikes, lies around 65 %; in resections for temporal lobe epilepsy (TLE) 60–90 % of patients achieve seizure freedom while in extra-temporal epilepsy it is around 40–65 % [40, 41]. We expected an increase in success percentage of 15 % leading to 80 % for HFOs based on retrospective studies in which part of the patients, with surgery based on spikes, had incomplete removal of HFO tissue and poor outcome [18], while incomplete removal of spikes does not predict seizure recurrence [15, 16]. We are aware that we chose a relatively large effect size. An overestimation of the success rate for the outcome in the HFO arm could lead to non-significant finding due to too a small population. Before we started with this RCT, we retrospectively studied our own ioECoG data in order to validate previous findings [22]. We found good outcome (Engel 1A and 1B after 1 year) in 70 % of patients and tailoring based on FRs could have improved outcome in 15 % of these patients [22].

This study also gave rise to the question whether or not we need to discriminate between epileptic and physiological HFOs, as we found some FRs, although far away from the area of resection and in functionally eloquent areas such as the sensorimotor and Broca’s areas, after resection in two patients who were seizure-free and medication-free. This means that we have to be careful when assessing HFOs in eloquent areas. In our retrospective data analysis we found that residual FRs were strongly related to epileptic tissue and poor outcome, while for ripples we found no association [22].

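### The primary risk difference ignores the stratification factors, and the planned logistic adjustment is not tied to the 10-point limit: valid, but slightly conservative

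*Protocol article*

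**What the plan says.** - **Randomization:** "Stratification for participating site and epilepsy type (extra-temporal versus temporal lobe epilepsy) is performed using block randomization", with blocks of 2, 4 and 6. There are two sites, so four strata.
- **Sample size:** the assumed success rates are "in the control group (tailoring based on spikes) of 65" per cent and "the expected success in the experimental group (HFOs) of 80" per cent, with "a non-inferiority limit of 10" per cent. The basis is given as "Using a 1-sided 95 % confidence interval", and the result as "to acquire an 80 % power we need 39 patients per group".
- **Statistical methods:** the primary intention-to-treat comparison is a risk ratio and a risk difference with a 95 % confidence interval and a 1-sided chi-square test. No stratification factor is named for it. A logistic regression follows, whose first purpose is "to adjust for the stratification factors, by including site and epilepsy type as variables in analysis". The section does not say on what scale that result is reported, or whether it is set against the limit.
- **Considerations:** for temporal resections, 60–90 % "of patients achieve seizure freedom while in extra-temporal epilepsy it is around" 40–65 %.

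**The concern.** When allocation is balanced within prognostic strata, chance differences in case mix between the arms are largely removed. A crude risk difference benefits from that balance in its point estimate. Its usual standard error, however, still counts the variation between strata as noise, so the interval is wider than the design requires. Epilepsy type is prognostic on the article's own figures, so the effect should not be zero.

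The analysis that does respect the strata is a logistic regression, whose usual output is an odds ratio. The article gives no odds-ratio limit and does not mention converting the model to a risk difference. As written, the analysis that matches the randomisation has no stated role in the non-inferiority decision. If crude and adjusted results pointed in different directions, the plan would not say which one governs.

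At stake is a little power in a trial sized with almost none to spare, and clarity about which number decides.

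**Working it through.** **1. Reproduce the plan's figure.** Inputs from Sample size: control 0.65, HFO 0.80, limit 0.10, 1-sided α 0.05, power 0.80.

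n per arm = (1.645 + 0.842)² × (0.65×0.35 + 0.80×0.20) / (0.15 + 0.10)² = 6.18 × 0.3875 / 0.0625 = 38.3, rounded up to **39**.

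This matches. With 39 per arm, SE = √(0.3875/39) = 0.0997 and power = Φ(0.25/0.0997 − 1.645) = 80.6 %. The match shows that the limit is on the risk-difference scale and that the calculation ignores strata.

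**2. Variance with and without strata.** The article gives no stratum mix. I assume control rates by type that lie within the Considerations ranges and average 65 %, and a benefit of 15 points in each type. The temporal share w follows from the 65 % average. Site is not modelled, because no site-specific rates are given.

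Stratified variance = [w × (temporal control + HFO variances) + (1 − w) × (extra-temporal control + HFO variances)] / 39.

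For 75/55 with w = 0.5: 0.5 × (0.1875 + 0.09) + 0.5 × (0.2475 + 0.21) = 0.3675, so SE = √(0.3675/39) = 0.0971.

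- Power of the stratified analysis = Φ(0.25/SE_strat − 1.645).
- Power of the crude analysis = Φ((0.25 − 1.645 × 0.0997)/SE_strat), because the estimate actually varies with the stratified SE.
- n per arm for the stratified analysis replaces 0.3875 in step 1 with the stratified sum.

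| Control rate, temporal / extra-temporal | w | SE crude | SE stratified | Power crude | Power stratified | n per arm, stratified |
|---|---|---|---|---|---|---|
| 75 / 55 | 0.50 | 0.0997 | 0.0971 | 81.2 % | 82.4 % | 37 |
| 75 / 52.5 | 0.56 | 0.0997 | 0.0964 | 81.4 % | 82.8 % | 36 |
| 80 / 50 | 0.50 | 0.0997 | 0.0937 | 82.1 % | 84.7 % | 34 |

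The gain is 1.2 to 2.6 points of power, or 2 to 5 patients per arm. If the types hardly differ (60 against 65 %, half each), the between-type share of the variance is 0.025²/(0.625 × 0.375) = 0.003, and the gain is about nil.

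**3. Error at the limit.** Set HFO 10 points below control in each type. Actual 1-sided error of the crude test = 1 − Φ(1.645 × √(crude variance / stratified variance)).

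- 75/55: √(0.475/0.455) = 1.022, error 4.6 %.
- 75/52.5: error 4.6 % (0.0455).
- 80/50: √(0.475/0.430) = 1.051, error 4.2 %.

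Simulation (200,000 trials per scenario, 39 per arm) gave 4.5, 4.4 and 4.1 % in the same order.

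**4. Choice of stratified interval.** In the same simulations a simple stratified Wald interval had 5.5–5.6 % error with two strata. With four assumed site-by-type strata (14, 15, 6 and 4 patients per arm) it reached 6.2 %, against 4.6 % for the crude interval. A stratified Miettinen-Nurminen score interval held 4.9–5.2 %.

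**5. Odds ratio against the limit.** A 10-point loss from control rate p equals an odds ratio of [q/(1−q)] / [p/(1−p)], with q = p − 0.10. This gives 0.643 at 40 %, 0.667 at 60 %, 0.658 at 65 %, 0.619 at 75 %, 0.583 at 80 % and 0.444 at 90 %. No single odds-ratio limit stands for 10 points across the article's 40–90 % range, so the model has to be converted to a risk difference before it is set against the limit.

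**The case against.** The best defence is that nothing stated is wrong. A crude risk difference is valid under stratified randomisation, and it matches the unstratified sample-size formula. Adjustment for both factors is planned. The article never says that the model will be reported as an odds ratio, and its reporting scale could be settled in a statistical analysis plan that is not shown. The gain is small and depends on an assumed mix, and power here hangs far more on the assumed 15-point advantage, which the authors themselves call large. A careless remedy can also do harm, as the Wald results show.

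Most of this stands, and it limits the point. What remains is that Statistical methods goes into detail. It names the primary estimators, the test, the adjusted model and its covariates, and gives a reason for not using a mixed model. Within that detail it leaves the strata out of the primary comparison and leaves the adjusted one without a link to the limit.

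A reader might infer three stronger things that the article does not support:

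- *That the crude analysis risks a false claim of non-inferiority.* The error runs the other way, below 5 %.
- *That the adjusted analysis is of no use for the primary conclusion.* The same logistic model yields a risk difference by standardisation. Only an unconverted odds ratio cannot be read against the limit.
- *That stratifying would lift power to around 90 %.* That needs a split of 90 against 40 %, the outer ends of the quoted ranges. A uniform 15-point benefit would then put temporal HFO patients at 105 %, which is impossible.

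**Conclusion.** The point holds as one of efficiency and clarity. The primary analysis does not use the factors the trial randomises by, and the analysis that does is not connected to the 10-point limit. The planned crude analysis is valid and slightly conservative: about 4.1–4.6 % actual 1-sided error instead of 5 %, with a typical loss of about 0–3 points of power. The sample size of 39 per arm is not in error.

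These sizes rest on an assumed mix with about half the patients temporal, control rates by type within the quoted ranges and averaging 65 %, and the same absolute effect in both types. They leave out any effect of site. The simulated power advantage of a simple stratified Wald interval should not be credited in full, since part of it comes from its excess error. The change is worth making because it costs almost nothing, not because the present plan would mislead.

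**What to change.** 1. Make the primary estimate a risk difference stratified by site and epilepsy type, with a stratified Miettinen-Nurminen score interval. Do not use a simple stratified Wald interval, which is liberal at this size. The alternative is a standardised risk difference from the logistic model already planned. Name one of the two in advance.
2. State that non-inferiority is decided by comparing its 1-sided 95 % lower bound with −10 points.
3. Fix before the outcome data are seen when strata will be collapsed over site, with a numerical threshold, keeping epilepsy type.
4. Keep the crude risk difference as a sensitivity analysis.
5. If the logistic route is chosen, say which missing-data rule applies. The article plans multiple imputation in the logistic regression and none for the primary endpoint.

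The cost is a change of analysis wording. No further data are needed, because both factors are recorded at randomisation, and the sample size can stay as it is.

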### Safety aspects

Adverse events (AEs) are defined as any undesirable experience occurring to a subject during the study, whether or not considered related to the experimental treatment. A SAE is defined as any untoward medical occurrence or effect that results in death, is life-threatening, requires (prolonged) hospitalization, results in persistent or significant disability or incapacity, or is a new event of the trial that is likely to affect the safety of the subjects. We will not report the majority of direct postsurgical complaints, such as nausea, headache, abdominal pains or pain related to the surgical scar during the hospitalization period, as AEs, as those result directly from brain surgery and will resolve before discharge. Similarly, direct post-operative functional deficits, due to surgically induced cerebral edema, will often resolve prior to discharge; these will not be reported as (S)AE. SAEs will be closely monitored by the researchers within the timeframe of hospital admission (normal range ≤ 10 days after surgery). The neurological deficits will be assessed with the NIHSS questionnaire (see also neurological deficits). During the 1 year follow-up period all reported AEs and SAEs, independent of the site, will be registered by the researchers and reported to the DMC. SAEs are reported to the Medical Ethics Committee.

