Secondary outcome parameters are:Volume of resected tissue (in cm^3^): the volume of resected tissue is determined by voxel-based volumetrics of the routine pre-surgical and post-surgical 3D whole head T1 magnetic resonance imaging (MRI) scan.Neurological deficits: neurological deficits are assessed by neurological examination and translated into the National Institutes of Health Stroke Scale (NIHSS) before surgery and before hospital discharge after surgery. The cumulated NIHSS score ranges between 0 and 42; a difference of 1 point on the NIHSS scale between the 2 tests is considered clinically relevant. In that case the NIHSS will be repeated at follow-up moments. Additionally, neurological deficits will be classified as “pre-existing” (either improved or aggravated) or as “new” (either anticipated or unexpected).Duration of surgery: post-hoc analysis of duration of surgery (start-stop time neurosurgeon, in minutes) and ioECoG recording time (in minutes).Surgical complications: accounts are kept of the number of (post-) operative complications, such as bleeding, infection, unexpected or aggravated neurological deficits. These events will also be reported as (serious) adverse events ((S)AE).Cognition: comparison of results from pre-operative and 12-month post-operative neuropsychological evaluation. This routine neuropsychological evaluation includes testing of IQ, working memory and processing speed. All tests performed are chosen according to the age of the patient, but report on the same domains. Per domain individual patients’ results will be dichotomized into negative, no, or positive change compared to pre-surgical baseline.Quality of life (QoL): QoL will be determined pre-operatively, and post-operatively after 6 to 8 weeks, and 6 and 12 months using a visual analog scale (VAS) on overall self-perceived quality of life, or by the parents in case of children < 12 years of age.

Data collection, management and storage is done in open source clinical trial software OpenClinica (OpenClinica, LLC, Waltham, MA, USA; www.openclinica.com), managed by the IT division of the Neurology and Neurosurgery Department of the UMC Utrecht. Figure 1 shows the timeline of the study procedures.

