### Interim analysis

Safety and efficacy analysis will be performed by the statistician of the independent Data Monitoring Committee (DMC) after the first 20 and 40 included patients. This analysis will be based on the available, preliminary, post-surgical outcomes and also includes the number of surgical complications and (serious) adverse events ((S)AE). The DMC can advise on premature termination of the study in case of harmful effects, or superiority, in one of the treatment arms or in case of non-feasibility issues.

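### The (S)AE rules in Outcomes and Safety aspects conflict for unexpected or aggravated neurological deficits attributed to cerebral oedema, and the exemption has no resolution condition

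*Protocol article*

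**What the plan says.** Four parts of the Methods bear on this point.

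- **Outcomes, surgical complications.** The list of complications to be counted runs "such as bleeding, infection, unexpected or aggravated neurological deficits. These events will also be reported as (serious) adverse events". No exception is made for cause or for early recovery.
- **Safety aspects, exemption.** After exempting routine post-surgical complaints, the section adds that "direct post-operative functional deficits, due to surgically induced cerebral edema, will often resolve prior to discharge; these will not be reported as (S)AE".
- **Safety aspects, SAE definition.** An SAE includes an event that "requires (prolonged) hospitalization, results in persistent or significant disability or incapacity". AEs are defined without regard to whether the treatment caused them.
- **Outcomes, neurological deficits.** Independently of any AE label, the neurological examination is "translated into the National Institutes of Health Stroke Scale (NIHSS) before surgery and before hospital discharge after surgery", and "a difference of 1 point on the NIHSS scale between the 2 tests is considered clinically relevant". After such a difference the NIHSS is repeated at follow-up. Deficits are also classed as pre-existing (improved or aggravated) or new (anticipated or unexpected).

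The Interim analysis section states that the DMC's review, after 20 and 40 patients, "also includes the number of surgical complications and (serious) adverse events". Safety aspects sends AEs and SAEs reported during the follow-up year to the DMC, and SAEs to the ethics committee. The Blinding section states that treating physicians and neurosurgeons cannot be blinded.

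**The concern.** Staff who follow Outcomes would report an unexpected, oedema-attributed deficit. Staff who follow Safety aspects would not. Both would be acting within the protocol, and (S)AE counts would then depend on which section was applied.

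The exemption also rests on a judgement of cause rather than on what happened to the patient. Telling oedema from an effect of the resection is a matter of opinion soon after surgery, and the staff closest to the patient at that time know the allocation. The article does not say who makes the attribution.

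What is at stake is the consistency of safety reporting. The Background names safety among the things the trial investigates, and the DMC may advise stopping for harm.

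**Working it through.** No figure in the plan is in dispute, so the check is a comparison of the texts. The table applies each rule to each kind of deficit seen directly after surgery.

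| Deficit | Outcomes (complications) | Safety aspects (exemption) | Result |
|---|---|---|---|
| A. Unexpected or aggravated, not attributed to oedema | Report | Exemption does not apply | Consistent |
| B. Unexpected or aggravated, attributed to oedema, resolved before discharge | Report | Do not report | Opposite instructions |
| C. As B, but still present at discharge | Report | Do not report, as written | Opposite instructions; also conflicts with the SAE definition where its criteria are met |
| D. Anticipated and new, attributed to oedema | Not named in the complications list | Do not report | No conflict with the complications list |

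**Why C falls under the exemption.** The sentence says that such deficits often resolve before discharge and then exempts them as a class. *Often* describes the class; it is not a test that each deficit must pass. The sentence before it exempts routine complaints on the firmer ground that they will resolve before discharge. For deficits the ground is weaker, but the exemption is just as categorical.

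**Why C conflicts within Safety aspects.** The SAE definition is about consequences: a longer stay, or disability that persists or is significant. A deficit still present at discharge can meet either criterion whatever its cause. The exemption removes it because of its presumed cause.

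**Where the effect ends.**

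1. *(S)AE reporting to the DMC and the ethics committee.* Directly affected for B and C.
2. *Complication count seen by the DMC.* Possibly affected. The exemption names only (S)AE reporting, which suggests the count is intact. But Outcomes says the complications are also reported as (S)AEs, so a deficit withheld from one list might be left out of the other. The text does not settle this.
3. *NIHSS secondary outcome.* Not affected. It is scored before surgery and before discharge in both arms and needs no AE label.

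**Size.** The article gives no rate of early deficits and no share attributed to oedema. The number of events in B or C cannot be derived, and any figure would be invented.

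**The case against.** The strongest reply is that this is a general rule with a narrow exception. Safety aspects refers the reader back to neurological deficits when it mentions the NIHSS, so the sections are meant to be read together. The exempt class is limited to direct deficits due to oedema, most of which are expected to pass. On that reading, row B is settled in favour of not reporting. This is a fair reading, but neither section says that one limits the other on reporting. It also leaves row C untouched: an exception without a resolution condition still collides with the SAE definition beside it.

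A reader might infer more than the text supports, and on these points the reply stands:

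- *That the sections conflict on post-operative deficits generally.* They do not. Row A is consistent, and row D is no conflict with the complications list.
- *That the DMC would not see these deficits.* This is not shown. The DMC also receives the number of surgical complications, and nothing says that exempt deficits leave that count. That the NIHSS is not named among the DMC's data is no fault in a condensed article.
- *That the comparison of deficits between arms is compromised.* It is not, because deficits present at discharge enter the NIHSS outcome in both arms.
- *That oedema labelling will differ by arm.* This is a possibility only. The article does not say that unblinded staff make the attribution, and it does blind the outpatient physicians, neurologist and psychologist involved in follow-up.

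**Conclusion.** The point holds in a limited form. For an unexpected or aggravated deficit seen directly after surgery and attributed to oedema, the two sections give opposite (S)AE instructions. As written, the exemption extends to deficits that persist to discharge, against the section's own SAE definition. Both rules are stated in the article, so this is a collision in the text and not a detail left to the full protocol.

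The consequence is inconsistent (S)AE reporting to the DMC and the ethics committee, and possibly an inconsistent complication count. The primary outcome and the NIHSS outcome are untouched. The size in events is unknown.

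The conclusion rests on two readings: that *often* is descriptive and not a condition, and that the complications item in Outcomes means what it says in making no exception. Concern about judgement influenced by allocation rests on the further assumption that unblinded staff make the attribution, which the article leaves open. The passages should be reconciled; the matter does not threaten the trial's main conclusion.

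**What to change.** Reconcile the two sections with one reporting rule based on documented recovery:

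- In Safety aspects, limit the (S)AE exemption to direct post-operative deficits that the planned pre-discharge NIHSS shows to be back to the pre-surgical baseline.
- State that an unexpected or aggravated deficit still present at that examination is counted as a complication and reported as an (S)AE, whatever its presumed cause.
- Keep the distinction in Outcomes between anticipated and unexpected new deficits; the change should not sweep anticipated deficits into the complications list.
- Put the same exception, by cross-reference, in the complications item in Outcomes, and say whether a resolved deficit remains in the complication count.

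This changes reporting only, not patient care. The cost is a short wording change and a few more AE forms, since the examination is already scheduled before discharge. It also removes the need to settle who attributes a deficit to oedema, because cause no longer decides reporting. It does not by itself make the assessment blinded: the article does not say who performs the pre-discharge examination.
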